#### LSAS

This instrument is used to assess patients’ fear in a range of social interactions and performance situations. The scale consists of 24 items, which are categorized into the following 2 elements: performance anxiety (13 items) and social situations (11 items). Scores are between 0 and 144, with higher scores indicating higher social anxiety [36].

#### EQ

The EQ is a 20-item self-report measure using a 5-point Likert scale ranging from 1 (*never*) to 5 (*always*). The total score is between 20 and 100. The scale focuses on decentering, defined as the ability to view the self as separate and different from own thoughts, the capacity for not reacting to negative experiences, and the ability to be self-compassionate. The EQ has been found to be reliable, and convergent and discriminant validities are established for both general and clinical samples. The EQ is also internally consistent, with temporal stability over a 1-month period and good convergent validity [37,38].

#### SF-36

The SF-36 is a 36-item multipurpose health survey to evaluate 8 health domains of functional health and the level of well-being, as well as physical and mental health summary measures and a health utility index. Possible scores for each domain range from 0 to 100, with higher scores indicating a better health status [39].

#### SPANE

This measure is a 12-item scale to assess positive experiences (6 items) and negative experiences (6 items). Because of the generality of items included in the scale, it can not only assess pleasant and unpleasant emotional feelings that are the focus of most scales, but also reflect other conditions, such as interest, flow, positive engagement, and physical pleasure. The positive (SPANE-P) and negative (SPANE-N) scale scores range between 6 and 30. Higher scores indicate a higher positive or negative affective status. The score obtained on subtracting the negative score from the positive score is called the SPANE-B score, which is between −24 and 24 [40].

#### RSES

This is a brief self-rated assessment tool to evaluate self-esteem, self-worth, acceptability, and confidence. It is the most recognized and widely used measure for these metrics. It has 10 items with a Likert scale (1 = *strongly disagree*, 4 = *strongly agree*). The total score ranges from 10 to 40, with higher scores indicating better self-esteem [41].

#### FFMQ

This tool is a self-report questionnaire that assesses mindfulness. It includes 5 factors, which are extracted on the basis of a factor analysis of 5 mindfulness questionnaires developed independently. The 5 facets are observing, describing, acting with awareness, not judging one’s inner experience, and not reacting to one’s inner experience. The total score ranges from 39 to 195, with higher scores representing a better mindfulness status [42].

#### CDRISC

The CDRISC is a brief self-rated assessment to measure resilience. The scale contains 25 items, all of which feature a 5-point Likert scale (4 = *true nearly all of the time*, 0 = *not true at all*). The scale is rated based on how the subjects felt over the past month. The total score ranges from 0 to 100, with higher scores reflecting greater resilience [43].

#### SCS

This scale assesses a person’s ability to be kind and understanding toward themself, as opposed to harsh and self-critical in instances of pain or failure. It includes 29 items and produces scores on 5 subscales (self-kindness, self-judgment, common humanity, isolation, mindfulness, and overidentification). The subscale scores represent the mean of each subscale’s item scores. Participants are asked to answer how often they had certain thoughts and feelings (1 = *rarely* to 5 = *very often or always*). Therefore, each subscale score is between 1 and 5. Higher scores indicate more self-compassion [44].

#### QIDS

The QIDS is a self-rated questionnaire to assess depressive symptoms, which is widely used. The responses to 16 separate items on the QIDS are converted into 9 DSM-IV symptom criterion domains. The total score is between 0 and 27. Higher scores indicate higher levels of depressive symptoms [45].

#### GAD7

GAD7 was developed to ask patients how often they experienced a set of symptoms in the past 2 weeks. Respondents respond using 4 response options on a Likert scale (0 = *not at all* to 3 = *nearly every day*). In addition, an item assessing the duration of anxiety symptoms is included. Therefore, GAD7 scores are between 0 and 21. Scores of 5, 10, and 15 represent mild, moderate, and severe anxiety symptoms, respectively [46].

#### PSS

The PSS was designed to measure the degree to which situations in one’s life are appraised as stressful. The scale has the following 2 versions: the 14-item version (PSS-14) and the 10-item version (PSS-10), with 4 items removed from the 14-item version. We use the PSS-10 in this study. This scale assesses perceived stressful experiences or stress responses in the previous month. Each item is rated on a 5-point Likert scale (4 = *never*, 0 = *very often*) to identify positive experiences or responses. The total score ranges from 0 to 40, with higher scores representing higher stress levels [47].

#### WHO-HPQ

The WHO-HPQ is a self-report instrument designed to estimate the workplace costs of health problems in terms of self-reported sickness absence and reduced job performance (presenteeism). Presenteeism is measured using the following two questions: “On a scale from 0 to 10, where 0 is the worst job performance anyone could have at your job and 10 is the performance of a top worker, how would you rate the usual performance of most workers in a job similar to yours?” and “Using the same 0-10 scale, how would you rate your overall job performance on the days you worked during the past four weeks?” A low presenteeism score indicates poor performance [48].

#### SWLS

This scale is a 5-item self-reported questionnaire to evaluate the cognitive aspect of subjective well-being. Scores for each subscale range from 1 (*strongly disagree*) to 7 (*strongly agree*). The total score ranges from 5 to 35, with higher scores indicating higher satisfaction [49].

#### FS

This scale includes 8 items relevant to significant aspects of human functioning, ranging from positive relationships to feelings of competence, meaning, and purpose in life. Each item is answered on a 7-point scale that ranges from 1 (*strong disagreement*) to 7 (*strong agreement*). Possible scores range between 8 (*strong disagreement* with all items) and 56 (*strong agreement* with all items). Higher scores indicate that respondents viewed themselves positively in important areas of functioning [40].

#### MAIA

The MAIA is a self-report scale for experimental interoception research and for the assessment of mind-body therapies [50]. It is a 32-item self-report instrument to assess interoceptive awareness on the following 8 subscales: noticing, not distracting, not worrying, attention regulation, emotional awareness, self-regulation, body listening, and trusting. Each subscale has 3 to 7 items, each assessed on a 6-point Likert scale (0 = *never*, 5 = *always*). Scores for each subscale range from 0 to 5. Higher scores indicate better interoceptive awareness [51].

#### EQ-5D

EQ-5D is a standardized measure for assessing health-related quality of life. Applicable to a wide range of health conditions and treatments, it provides a simple descriptive profile and a single index value for health status. The score ranges between 0 (death) and 1 (perfect health) [52].

#### HAM-A

HAM-A is a rating scale used to measure the severity of anxiety symptoms. It includes 14 items that measure both psychiatric and somatic anxiety. Each item is scored from 0 (*not present*) to 4 (*severe*), with a total score between 0 and 56. HAM-A has a structured interview guide (Structured Interview Guide for Hamilton Anxiety Scale: SIGH-A) [53,54].

#### Interoception

To assess interoception objectively, we use a heartbeat detection task that has been used and validated worldwide. The participants are asked to wear a pulse oximeter on their finger, which is connected to a PC to evaluate their actual pulse. They are also asked to count the heartbeat felt during various measurement periods. Interoceptive accuracy is measured based on the discrepancy between the number of actual and reported heartbeats [55,56]. The validity and reliability of all measures of the original and Japanese versions, except the Japanese version of the PAS, have been confirmed [34-54,57-74]. With respect to the Japanese version of the PAS, although it shows sufficient reliability, the authors recommend using it as a secondary outcome, because the criterion-related validity indicates “relatively strong correlation” (ie, the correlation coefficient ranges between 0.48 and 0.68). We judge it to be sufficient for use as a secondary outcome.

### Schedule for Assessments

All participants will be requested to fill the self-report measures at 4 weeks (the intervention midpoint) and 8 weeks (postintervention), and at 3, 6, and 10 months postintervention, as well as complete the baseline assessments. HAM-A and interoception will be assessed at baseline (0 weeks), at the end of the MBCT (8 weeks), and at 10 months postintervention. We will allow for a range of ±2 weeks from the scheduled evaluation date for the evaluation during the intervention period and ±4 weeks from the scheduled evaluation date for the evaluation during the follow-up period. For those who are unable to come to the hospital to complete the self-rated scales, we will contact them and ask them to fill out and return the above evaluation items by mail or telephone. The assessment schedule is presented in Table 2.

**Table 2 table2:** Schedule of assessments

	Study period																			
	Screening period	Intervention period									Follow-up period									
Timepoint		1 wk	2 wk	3 wk	4 wk	5 wk	6 wk	7 wk	8 wk	1 mo		2 mo	3 mo	4 mo	5 mo	6 mo	7 mo	8 mo	9 mo	10 mo
Screening (SCID^a^, etc)	✓																			
Informed consent	✓																			
MBCT with f/u^b^		✓	✓	✓	✓	✓	✓	✓	✓	✓		✓	✓	✓	✓	✓	✓	✓	✓	✓
MBCT without f/u^c^		✓	✓	✓	✓	✓	✓	✓	✓											
STAI^d^	✓				✓				✓				✓			✓				✓
PAS^e^	✓				✓				✓				✓			✓				✓
LSAS^f^	✓				✓				✓				✓			✓				✓
EQ^g^	✓				✓				✓				✓			✓				✓
SF-36^h^	✓				✓				✓				✓			✓				✓
SPANE^i^	✓				✓				✓				✓			✓				✓
RSES^j^	✓				✓				✓				✓			✓				✓
FFMQ^k^	✓				✓				✓				✓			✓				✓
CDRISC^l^	✓				✓				✓				✓			✓				✓
SCS^m^	✓				✓				✓				✓			✓				✓
QIDS^n^	✓				✓				✓				✓			✓				✓
GAD7^o^	✓				✓				✓				✓			✓				✓
PSS^p^	✓				✓				✓				✓			✓				✓
WHO-HPQ^q^	✓				✓				✓				✓			✓				✓
SWLS^r^	✓				✓				✓				✓			✓				✓
FS^s^	✓				✓				✓				✓			✓				✓
MAIA^t^	✓				✓				✓				✓			✓				✓
EQ-5D^u^	✓				✓				✓				✓			✓				✓
HAM-A^v^	✓								✓											✓
Interoception	✓								✓											✓
Health service use	✓				✓				✓				✓			✓				✓
Homework engagement		✓	✓	✓	✓	✓	✓	✓	✓	✓		✓	✓	✓	✓	✓	✓	✓	✓	✓

^a^SCID: Structured Clinical Interview for Diagnostic and Statistical Manual of Mental Disorders, 4th edition disorders.

^b^MBCT with f/u: mindfulness-based cognitive therapy with follow-up sessions.

^c^MBCT without f/u: mindfulness-based cognitive therapy without follow-up sessions.

^d^STAI: State-Trait Anxiety Inventory.

^e^PAS: Panic and Agoraphobia Scale.

^f^LSAS: Liebowitz Social Anxiety Scale.

^g^EQ: Experiences Questionnaire.

^h^SF-36: Short-Form 36-Item Health Survey.

^i^SPANE: Scale of Positive and Negative Experience.

^j^RSES: Rosenberg Self-Esteem Scale.

^k^FFMQ: Five Facet Mindfulness Questionnaire.

^l^CDRISC: Connor Davidson Resilience Scale.

^m^SCS: Self-Compassion Scale.

^n^QIDS: 16-item Quick Inventory of Depressive Symptomatology.

^o^GAD7: Generalized Anxiety Disorder Assessment-7.

^p^PSS: Perceived Stress Scale.

^q^WHO-HPQ: World Health Organization Heath and Work Performance Questionnaire.

^r^SWLS: Satisfaction With Life Scale.

^s^FS: Flourishing Scale.

^t^MAIA: Multidimensional Assessment of Interoceptive Awareness.

^u^EQ-5D: EuroQoL-5 Dimensions.

^v^HAM-A: Hamilton Anxiety Scale.

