### Interventions

#### MBCT With Follow-up Sessions Group

The patients in the intervention group will be offered an 8-week MBCT followed by a 10-month follow-up program. The MBCT consists of 8 weekly sessions in a group format. Each session lasts for 2 hours. In the program, participants practice mindfulness meditation as well as cognitive exercise. Minimum modifications have been made to the original version of MBCT [20] because the study targets patients with anxiety disorders rather than those with depression. Specifically, we have replaced psychoeducation of depression with that of anxiety. Table 1 describes the themes and contents of each session. The participants will be requested to practice mindfulness meditation for approximately 30 minutes daily and to record the duration of time they meditated and the meditation type.

**Table 1 table1:** Themes and content of the program.

Session	Theme	Content
1	Automatic pilot	Psychoeducation: What is mindfulness? Exercise: Mindfulness eating (“raisin exercise”)/body scan Homework: Mindfulness of a routine activity/body scan
2	Dealing with barriers	Psychoeducation: Association of mood and thoughts Exercise: Thoughts and feelings exercise/body scan/mindful breathing meditation Homework: Body scan/breathing meditation/pleasant events calendar
3	Mindfulness of the breath	Psychoeducation: Awareness of mind wandering and focusing on the breath Exercise: Breathing meditation/gentle yoga/mindful walking Homework: Breathing meditation/gentle yoga/mindful walking/unpleasant events calendar
4	Staying present	Psychoeducation: Staying present/about anxiety symptoms^a^ Exercise: Meditation of sounds and thoughts/breathing meditation Homework: Meditation of sounds and thoughts/breathing meditation/3-minute breathing space
5	Allowing/letting be	Psychoeducation: Exploring difficulty Exercise: Breathing meditation/meditation of sounds and thoughts/exploring difficulty Homework: Breathing meditation/meditation of sounds and thoughts/exploring difficulty/3-minute breathing space
6	Thoughts are not facts	Psychoeducation: Cognitive biases Exercise: Breathing meditation/meditation of sounds and thoughts/exploring difficulty Homework: Breathing meditation/meditation of sounds and thoughts/exploring difficulty/3-minute breathing space

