#### Clinical Outcomes

The primary clinical outcome is the mean and standard deviation of the STAI score in both groups at 8 weeks and 5, 8, and 12 months after the start of the intervention. The mean difference and standard deviation of the STAI score between the groups is also assessed.

The secondary clinical outcomes are PAS, LSAS, EQ, SF-36, SPANE, RSES, FFMQ, CDRISC, SCS, QIDS, GAD7, PSS, WHO-HPQ, SWLS, FS, MAIA, EQ-5D, HAM-A, and interoception scores (baseline, 8 weeks, and 12 months only for HAM-A and interoception); health service use; engagement in meditation practice; and satisfaction with and expectation of the classes.

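### The ±2-week window lets the 8-week assessment, defined as post-intervention, be taken from week 6, before the MBCT course has ended

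*Protocol article*

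**What the plan says.** The Schedule for Assessments section places the self-report measures "at 4 weeks (the intervention midpoint) and 8 weeks (postintervention") and at 3, 6 and 10 months after the intervention. HAM-A and interoception are placed "at the end of the MBCT (8 weeks"), besides baseline and 10 months after the intervention. The tolerance is then stated: "We will allow for a range of ±2 weeks from the scheduled evaluation date for the evaluation during the intervention period". In the follow-up period it is plus or minus "4 weeks from the scheduled evaluation date for the evaluation during the follow-up period".

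Table 2 opens with the headers "Screening period Intervention period", followed by the follow-up period. Its week columns, 1 to 8, belong to the intervention period, and MBCT is ticked in each of them. The Interventions section says: "The MBCT consists of 8 weekly sessions in a group format".

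The Clinical Outcomes section reports the STAI mean and SD "in both groups at 8 weeks and 5, 8, and 12 months after the start of the intervention". For the two rater-administered measures the time points are "baseline, 8 weeks, and 12 months only for HAM-A and interoception". The Statistical Analysis section enters visit in the mixed model as a category.

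**The concern.** The 8-week visit is defined by its content: it is the reading after the course. The tolerance is symmetric around a date and is not tied to the last session. It therefore accepts readings taken while the course is still running, and nothing in the article requires the 8-week form to follow session 8. Because visit is categorical in the model, a week-6 reading would be analysed as week 8 with no allowance for when it was taken.

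What is at stake is the meaning of the 8-week mean and SD. The trial exists partly to supply those figures for a definitive trial. If some readings come from mid-course, the reported post-treatment level mixes patients who have finished MBCT with patients who have not. HAM-A and interoception are the only measures with blinded raters, and for them week 8 is one of two post-baseline readings.

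**Working it through.** The plan gives no derived figure to reproduce. The check is interval arithmetic on the stated schedule.

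**Inputs.** Scheduled weeks 4 and 8, with ±2 weeks in the intervention period and ±4 weeks in follow-up (Schedule for Assessments). Eight weekly sessions (Interventions). Sessions ticked in weeks 1 to 8 (Table 2).

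**Windows in the intervention period.**
- Week 4: 4 − 2 = 2 to 4 + 2 = 6.
- Week 8: 8 − 2 = 6 to 8 + 2 = 10.

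The two windows share only the boundary at week 6. The overlap has zero length.

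**Sessions still to come at week 6.**
- Table 2's calendar (session k in week k): sessions 7 and 8 remain. Six of 8 sessions, or 75%, have been given.
- Session 1 on day 0 (session k at week k − 1): session 7 falls at week 6 and session 8 at week 7. Session 8 remains, and session 7 too if the form is completed before it.

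On either count, the early end of the window lies before the end of the course. On the second count the course ends at week 7, so readings from then on are properly post-course even though they precede week 8.

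**Alternative reading of the period.** If week 8 were treated as follow-up, ±4 weeks would give 8 − 4 = 4 to 8 + 4 = 12. That window is wider and opens earlier, so it does not remove the conflict.

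**Later visits.** With one month = 30.4375/7 ≈ 4.348 weeks, the visits at 3, 6 and 10 months after week 8 have these windows:
- 8 + 3 × 4.348 ± 4 = weeks 17.0 to 25.0
- 8 + 6 × 4.348 ± 4 = weeks 30.1 to 38.1
- 8 + 10 × 4.348 ± 4 = weeks 47.5 to 55.5

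None meets another, and none meets the 8-week window, which ends at week 10. The problem is confined to week 8.

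**The case against.** The strongest reply is that the section already says what the visit is. A tolerance can be read as slack around a visit understood to be post-course, and a sensible coordinator would not take it before the last session. The statistical analysis plan, which is not shown, may also hold rules for assigning forms to visits. This lowers the likely frequency of early readings. It does not remove the conflict, because the article states the window as a rule and the rule accepts such readings.

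Other replies limit the point, and they stand:

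- A reader might infer that the week-4 and week-8 visits overlap. They only touch at week 6, and week 4 is not a primary time point. Narrowing its window would be a preference rather than a correction.
- A reader might infer bias in the comparison of arms. Both arms are offered the same 8-week MBCT and are subject to the same window. Bias would need timing to differ by arm, and the documents describe no mechanism for that.
- A reader might infer that the judgement of lasting benefit is distorted because week 8 is its reference level. The planned analysis is of mean change from baseline at each visit, and no change from week 8 is specified. The 5-, 8- and 12-month comparisons with baseline do not use the 8-week reading as their reference.
- A reader might want a percentage for the understatement. That would need the share of early readings and the shape of improvement over the course, and the documents give neither.

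**Conclusion.** The point holds as a conflict between a stated window and the visit's own definition. The 8-week assessment can validly be taken from week 6, with at least session 8 outstanding, and with session 7 outstanding too on Table 2's calendar. This can blur the mean and SD at one of four primary time points, and at one of two post-baseline visits for HAM-A and interoception.

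The size cannot be computed from the documents. It depends on how many forms were completed before the final session and on how much patients change over the last one or two sessions. The conclusion rests on week 8 being in the intervention period, as Table 2 shows, but placing it in follow-up would not rescue it. Neither a built-in bias between arms nor damage to the later comparisons with baseline is supported. It is a cheap improvement worth making, not a flaw that threatens the trial.

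**What to change.** State that an assessment counts as the 8-week visit only if it is dated on or after the participant's final scheduled MBCT session and no later than the existing limit of 2 weeks after the scheduled date. Anchoring on the session, not on week 8 itself, works whichever way weeks are counted. The reading should preferably precede the start of app access in the follow-up arm. The apps are meant for the follow-up period and go to one arm only, so a reading late in the window could otherwise include them. The current window has the same exposure.

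Forms already completed cannot be repeated. By January 2021, 43 participants were enrolled, and the first group (n=20) had been offered the in-person course. For these data, flag every 8-week form dated before the final session. Then either exclude those forms from the 8-week summary or show the summary with and without them.

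The cost is one sentence and a check of dates. The downside is that a few 8-week values may be lost or moved to a sensitivity summary.

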### Sample Size

For a feasibility study that involves evaluating the standard deviation of continuous variables, a sample size of 24 to 50 cases is recommended [75,76]. Therefore, in this study, the maximum number of enrolled patients has been set to 50 (25 for each arm).

### Statistical Analysis

Statistical analyses and reporting of this trial will be conducted with primary analyses based on the intention-to-treat approach. The full analysis set will include all randomized subjects administered at least one procedure of the investigational treatment. For baseline variables, we will generate summary statistics with proportions and frequencies for categorical variables, and means and standard deviations for continuous data. Statistical data relevant to feasibility will be presented descriptively. For primary and secondary clinical outcome analyses, we will analyze mean changes from baseline with a restricted maximum likelihood-based repeated measures approach. The mixed model for repeated measures analyses will include the fixed and categorical effects of treatment, visit, and the treatment×visit interaction. We will employ Kenward-Roger approximation to estimate the degrees of freedom of the denominator. We will not conduct any adjustment for multiple testing of secondary outcomes because of the exploratory nature of the study. Imputation will not be performed for missing values because mixed models can deal with missing data by maximum likelihood. All comparisons are planned, and all P values are two-sided. A 5% significance level will be set for all statistical analyses. All statistical analyses will be conducted using Stata version 16 (Stata Corp).

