### Randomization

Eligible participants will be randomly allocated to either the augmented MBCT with follow-up sessions group or MBCT without follow-up sessions group (1:1 ratio). A computer-generated random number stratified by diagnosis (ie, panic disorder/agoraphobia and social anxiety disorder) and baseline score for the STAI will be assigned to each participant. The Project Management Office at Keio Center of Clinical Research, which is an independent institution from the study group, will manage the randomization process. The flow of the recruitment of participants is shown in Figure 1.

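### The repeated-measures model omits both stratification factors and every outcome's own baseline, so the between-group clinical comparisons are less precise than the design allows and conservative for STAI

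*Protocol article*

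**What the plan says.** Under Randomization, allocation is 1:1 and uses "A computer-generated random number stratified by diagnosis (ie, panic disorder/agoraphobia and social anxiety disorder) and baseline score for the STAI". The STAI cut-point is not given.

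Under Statistical Analysis, for primary and secondary clinical outcomes, "we will analyze mean changes from baseline with a restricted maximum likelihood-based repeated measures approach". The model terms follow: "The mixed model for repeated measures analyses will include the fixed and categorical effects of treatment, visit, and the treatment×visit interaction." The same section specifies Kenward-Roger degrees of freedom, no imputation and two-sided P values, and adds: "A 5% significance level will be set for all statistical analyses."

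Nowhere does the article add diagnosis, baseline STAI or a scale's own baseline score to the model. Baseline enters only as the value subtracted to form the change.

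**The concern.** Stratified randomisation makes the arms more alike on diagnosis and baseline STAI than chance alone would. A model without those factors still counts their variation as noise, so its standard error is larger than the real sampling error of the contrast.

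Taking change from baseline does not cure this. Subtraction fixes the slope on baseline at 1. For any baseline-to-follow-up correlation below 1, change stays correlated with baseline. Precision is then lost, and a chance baseline difference on a scale that was not stratified is over-corrected.

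At stake are the intervals and P values for the between-group clinical comparisons. The article makes comparing clinical outcomes between arms one of its two stated purposes (Rationale for the Study) and tests them at the 5% level.

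**Working it through.** **The plan's own figure.** The maximum of 50 is 2 × 25 and lies within the cited range ("a sample size of 24 to 50 cases is recommended"). It rests on no effect size, SD or power, so there is nothing to recompute, and the model terms do not affect it.

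**Inputs.** From the article: 1:1 allocation, the two stratification factors, change from baseline as the response, the three model terms, a two-sided 5% level, and 43 enrolled by January 2021 (Results). Assumed: baseline-to-follow-up correlation ρ = 0.3, 0.5 or 0.7, equal variance σ² at both times, and STAI split at the median. The closed form below also assumes no diagnosis effect and exact balance within strata. With complete data and an unstructured covariance, the contrast at one visit is a comparison of change scores at that visit.

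**Formulas.**
- Nominal variance of change: 2σ²(1−ρ).
- Variance after adjusting for continuous baseline: σ²(1−ρ²). Relative to nominal this is (1+ρ)/2.
- Squared correlation of change with baseline: (1−ρ)/2. A median split captures 2/π of it.
- True STAI variance under stratification, relative to nominal: 1 − (2/π)(1−ρ)/2. The model SE is too large by one over the square root of this.

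| Quantity | ρ = 0.3 | ρ = 0.5 | ρ = 0.7 |
|---|---|---|---|
| Captured by the median split | 0.223 | 0.159 | 0.095 |
| True / nominal variance, STAI | 0.777 | 0.841 | 0.905 |
| Model SE / true SE, STAI | 1.13 | 1.09 | 1.05 |
| Approximate type I error | 2.6% | 3.3% | 3.9% |
| Adjusted / nominal variance | 0.65 | 0.75 | 0.85 |
| Adjusted / true variance, STAI | 0.84 | 0.89 | 0.94 |

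The last row is the fifth divided by the second, for example 0.65/0.777 = 0.84. The true STAI variance therefore falls by about 16%, 11% and 6%. For a scale unrelated to the strata, true and nominal variance coincide, so the full 35%, 25% and 15% applies.

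**In participants, at 43 enrolled.** STAI: 43/0.84, 43/0.89 and 43/0.94 give about 51, 48 and 46, a gain of roughly 8, 5 and 3. A scale the strata do not balance: 43/0.65, 43/0.75 and 43/0.85 give about 66, 57 and 51, a gain of up to 23, 14 and 8.

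**Simulation check.** 20,000 null trials per setting, n = 48, permuted blocks of 4 within four strata (block size assumed), with a diagnosis effect of 0 or 0.5 SD:
- Three-term model: SE too large by 12–14% (ρ = 0.3), 7–11% (0.5) and 4–9% (0.7). Type I error is 2.5–2.7%, 2.9–3.5% and 3.3–4.3%.
- With diagnosis and continuous baseline STAI added: model SE / true SE is 0.99–1.00 and type I error 4.9–5.1%.
- Power for a 0.5 SD effect, with a 0.5 SD diagnosis effect (8,000 trials): from 36% to 49% at ρ = 0.5, and from 54% to 65% at ρ = 0.7.

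**Chance imbalance on other scales.** With 43 patients, the SE of a baseline difference on a scale not balanced by the strata is √(4/43) = 0.30 SD. An imbalance of that size shifts an unadjusted change score by (1−ρ) × 0.30, which is 0.15 SD at ρ = 0.5. Adjusting for that scale's own baseline removes the shift.

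**The case against.** The best defence is that this is a feasibility trial with no power target. The error is on the safe side, secondary outcomes are labelled exploratory, and a fuller analysis plan may list more terms. The phrase about fixed and categorical effects also does not strictly exclude a continuous baseline covariate. Much of this stands, and it limits the weight of the point. It does not remove it: the article lists the model's terms, and diagnosis, which is categorical, is not among them. A fuller plan with other terms would differ from this text.

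Four stronger readings are tempting, and the article does not support them.
- *A reader might infer that the SDs reported as primary outcome 4 are inflated.* They are raw means and SDs at each time point, presented descriptively. Model covariates do not change them.
- *A reader might infer that the P values are anti-conservative.* The SE error is upward only, and for scales weakly related to the strata it is small. The issue for those scales is lost precision.
- *A reader might apply the 35%, 25% and 15% reductions to STAI.* Those figures compare with the nominal change-score variance. Stratifying on STAI already removes part of that variance, which leaves 16%, 11% and 6%.
- *A reader might say the other scales have no protection against imbalance.* Diagnosis is a stratum and bears on PAS and LSAS, and scales correlated with STAI gain partial balance. Averaged over randomisation, the change score is unbiased; the bias is conditional on the imbalance that occurs.

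**Conclusion.** The omission is real and should be corrected, but it is not critical. As written, the model overstates the STAI standard error by about 13%, 9% or 5% at ρ = 0.3, 0.5 or 0.7, and by somewhat more if diagnosis also predicts change. It forgoes about 16%, 11% or 6% of the true variance of the STAI contrast, and up to 35%, 25% or 15% on scales that the stratification leaves unbalanced. These sizes depend on ρ, the STAI cut-point and the diagnosis effect, none of which the article gives. The direction for STAI does not depend on the exact values: for any ρ below 1, effective stratification on baseline STAI makes the unadjusted standard error too large. The consequence is confined to the between-group clinical comparisons.

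**What to change.** Replace the sentence listing the model terms with:

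> The MMRM will include treatment, visit, treatment×visit, diagnosis stratum, the baseline value of the outcome and baseline×visit; models for outcomes other than STAI will also include baseline STAI.

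In the STAI model, baseline STAI then enters once, as a continuous covariate. Listing it both as the outcome's baseline and as a stratification factor would duplicate it.

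For planning the definitive trial, report the residual SD and baseline correlation from this model alongside the raw SDs, not in place of them.

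The cost is a few degrees of freedom. Every score needed is already in the baseline assessment schedule, so no new data are required. The article describes data collection as continuing to May 2022, so the wording could be settled before analysis.
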